### Methods in analysis to handle protocol non-adherence and any statistical methods to handle missing data {20c}

During the data collection process, efforts will be made to minimize missing data occurrence. Should missing data occur, the numbers (with percentages) of losses to follow-up (defaulters and withdrawals) will be reported by randomized group at each assessment time point. If possible reasons why the data are missing will also be reported. Missing data will not be imputed in anyway.

The primary analysis will be based on an intention-to-treat (ITT) population. An unadjusted analysis of the primary outcome will also be performed on the per-protocol (PP) population. This will exclude patients stopping or pausing the study medication at any time point and those withdrawn from the trial.

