### Sample size {14}

The primary hypothesis is that adjunct corticosteroid treatment will reduce mortality in the intervention arm by ~25% (relative measure). This is a conservative measure as the studies described in the background report relative risk reductions of between 33% and 61%. Observational data indicates 30% in-hospital mortality among based on data collected from CIN hospitals in the past one year and Kilifi County Hospital over a period of 5 years
^
24
^. We have made a conservative assumption that 30-day mortality in the control arm of the trial will be 20% and that 30-day mortality in the intervention arm will be 15%. Allowing for 5% loss to follow-up, a sample size of 1,090 patients per study arm (total 2,180 patients, ~ 390 deaths) will achieve statistical power of 85%, with a 2-sided type 1 error rate of 5%.

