## Data collection and management

### Plans for assessment and collection of outcomes {18a}

Trial staff will be trained on data quality and the necessary data to be collected for trial participants. Basic sociodemographic and clinical data for the participants will be collected from their medical records while in the hospital.

The trial staff will not conduct additional medical assessments but will record findings from assessment done the attending clinical team.

The main trial outcome is vital status (dead or alive) at 30 days after enrolment. Outcome data will be collected via phone call if the participant will have been discharged from the hospital. For participants who are still in-patient by the 30
^th^ day of participation, outcome data will be recorded on the same day in-person.

Data will be abstracted on to electronic case report forms (eCRFs). Regular data checks will be conducted on the database to ensure completeness of the data.

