## Statistical methods

### Statistical methods for primary and secondary outcomes {20a}

The primary analysis will be an intention to treat analysis in which we will compare outcomes between all patients randomized to the two study arms, irrespective of whether they receive their allocated treatment. For the primary outcome of 30-day mortality, we will use the unadjusted hazard ratio determined from Cox regression to estimate the mortality rate ratio between the treatment groups. If we detect any imbalances in potential confounders at baseline (such as age, sex, severity of illness, study site), then an adjusted Cox model will be used. If losses to follow-up do occur, patients will be censored at time of last assessment. Kaplan-Meier survival curves will be constructed to display cumulative mortality over the 30-day follow-up period.

In the per-protocol analysis we will exclude patients stopping or pausing the study medication at any time point and those withdrawn from the trial.

Complete case analyses will be used for secondary endpoints. For all secondary endpoints, we will calculate unadjusted and adjusted estimates of the effect size and corresponding 95% confidence intervals using linear, logistic, or cox proportional hazards regression as appropriate. All analysis will be done using R (Version 4.4.2, R Foundation for Statistical Computing: Vienna, Austria)

For the immunology outcome, omics data such as proteomic and transcriptomic data generated will be processed in the R programming language as described in section 33. To find genes/proteins whose mean response has significantly changed over the first 72 hours, the processed data will be fitted in a multinomial mixed model predicting the possible outcomes, adjusting for relevant baseline characteristics. The expected outcomes are, survived versus died in the treatment and placebo arms.

To understand the biological response associated with survival, induced/repressed by the treatment, functional analysis of the significant genes/proteins will be explored using R packages such as Clusterprofiller, GSVA and fgsea.

Integrative approaches will be used on the cellular phenotyping, proteomic, transcriptomic, metabolomic data to elucidate the biological processes promoted/repressed by corticosteroid treatment that are associated with survival that could be targeted with additional intervention

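### The unconditional ban on imputation makes adjusted models drop participants with an unrecorded covariate, chiefly severity, and bars imputation-based checks on unknown 30-day vital status

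*Protocol article*

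**What the plan says.** Section {20c} of the protocol article requires losses to follow-up to be reported by arm at each time point, with reasons where possible. It then states: "Missing data will not be imputed in anyway". No exception is made for baseline covariates or for sensitivity analyses.

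Three other provisions interact with that sentence:

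- Section {20a} makes the primary analysis an unadjusted Cox model in everyone randomised. If baseline imbalance is found, an adjusted Cox model is to be used. Its example covariates are age, sex, severity of illness and study site. Section {20b} adds adjusted analyses for gender, hospital location and age, with an open list of further confounders.
- Section {18a} takes baseline sociodemographic and clinical data from the medical record and adds: "The trial staff will not conduct additional medical assessments but will record findings from assessment done the attending clinical team".
- For the outcome, Section {20a} says: "If losses to follow-up do occur, patients will be censored at time of last assessment".

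**The concern.** **Covariates.** Severity is known only where the ward wrote it down. With imputation barred, a standard Cox or logistic fit discards each participant with a missing covariate. If imbalance triggers the adjusted model for the primary outcome, that model may no longer compare all randomised patients, although Section {20a} defines the primary analysis on that set. The loss need not be random, because how fully a chart is completed can depend on how ill the patient is and on the hospital.

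**Outcome.** Censoring at last assessment assumes that patients not reached die at the same rate as comparable patients still followed. Median admission is 4 days (Section {8}) and post-discharge contact is by calls on days 14 and 30 (Section {13}). A patient reached at neither call would therefore be censored near discharge. Death is a plausible reason for not being reached. The usual ways to test the assumption (best and worst case, tipping point, delta-adjusted multiple imputation) all assign values to missing outcomes, so the sentence excludes them. A statistical analysis plan that added one would contradict the protocol.

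**Working it through.** **Inputs from Section {14}:** 30-day mortality 20% (control) and 15% (intervention), power 85%, two-sided 5%, 5% loss to follow-up, 1,090 per arm. **Assumed, because the documents give no figure:** the proportion with a missing covariate, and mortality among the lost.

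**1. Reproduce the design.** Pooled two-proportion formula, no continuity correction:

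n = [1.960 × √(2 × 0.175 × 0.825) + 1.036 × √(0.20 × 0.80 + 0.15 × 0.85)]² / 0.05² = 1,035.5 per arm.

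Dividing by 0.95 gives 1,090, as stated. Power at 1,035.5 evaluable per arm (2,071 in total) is 85.0%.

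**2. One incomplete covariate.** If a proportion m lacks it, 1,035.5 × (1 − m) per arm remain:

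| Missing (assumed) | Kept of 2,071 | Dropped | Power |
|---|---|---|---|
| 0% | 2,071 | 0 | 85.0% |
| 5% | 1,967 | 104 | 83.2% |
| 10% | 1,864 | 207 | 81.1% |
| 20% | 1,657 | 414 | 76.4% |

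These figures ignore any precision gained by adjusting. An events-based check with hazard ratio ln(0.85)/ln(0.80) = 0.728 and 2,071 × 0.175 = 362 deaths starts at 85.5% and gives 83.7%, 81.7% and 77.0%.

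**3. Unknown vital status.** About 5% of 1,090 is 54 lost per arm, leaving 1,036 observed. Take 207 observed control deaths (20.0%) and let 11 of 54 lost controls die (about 20%), so the control total is 218/1,090. Vary deaths among the lost intervention patients and apply a pooled two-proportion test, as a simple stand-in for the Cox model:

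| Observed result | Lost intervention deaths | Intervention total | p |
|---|---|---|---|
| 155 v 207 of 1,036 (15.0% v 20.0%) | not assigned | – | 0.003 |
| same | 16/54 (30%) | 171/1,090 | 0.009 |
| same | 27/54 (50%) | 182/1,090 | 0.046 |
| same | 28/54 (52%) | 183/1,090 | 0.053 |
| 166 v 207 of 1,036 (16.0% v 20.0%) | not assigned | – | 0.019 |
| same | 16/54 (30%) | 182/1,090 | 0.046 |
| same | 17/54 (31%) | 183/1,090 | 0.053 |

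**4. Equal mortality among the lost.** If 16 of 54 die in both arms, the totals are 171 v 223 (p = 0.004) and 182 v 223 (p = 0.024). Both results survive, so a difference between arms in mortality among the lost is what matters.

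**The case against.** Much of the opposing case stands.

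- A reader might infer that every adjusted model loses patients. The documents do not support that. Hospital is known for everyone because randomisation lists are site-specific, age is needed for eligibility, and sex should be near-complete. Of the covariates named, only severity is plausibly incomplete.
- A reader might compound missingness over several covariates and reach a far larger loss. Section {20a} offers four examples and Section {20b} names three, nearly all of them likely complete, so nothing in the documents supports such a scenario.
- A reader might infer that the trial's primary result is not intention-to-treat. The unadjusted Cox model needs no covariates and keeps lost patients until they are censored. Only an adjusted model that drops incomplete records leaves the full randomised set.
- A reader might infer that no check on loss to follow-up is possible. Inverse-probability-of-censoring weighting imputes nothing, and losses by arm must be reported.
- Setting 5% loss beside a 5-point effect compares unlike quantities. The distortion is roughly 5% times the between-arm difference in mortality among the lost.
- Follow-up is well supported: daily inpatient review, calls to next of kin, at least three contacts per participant and clinic tracing.

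Two arguments go less far. The sentence follows text on losses to follow-up and might be read as covering outcomes only, and a missing-category term is arguably not imputation. But the wording has no limit, and filling in a covariate by mean or model would breach it. It is also true that a protocol article may leave sensitivity analyses to a statistical analysis plan, and their absence here is no fault. The fault is a stated rule that such a plan could not depart from without contradicting the protocol.

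**Conclusion.** The point holds in limited form. Followed as written, the rule lets an adjusted model lose randomised participants through an incompletely recorded covariate, chiefly severity, and this can include the model used for the primary outcome if imbalance is found. It also leaves non-informative censoring without an imputation-based check.

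The size is modest at low missingness: 1.8 points of power at 5% missing and 3.9 at 10%, rising to 8.6 at 20%, all under assumed rates for a single covariate. The design effect is robust to the planned loss unless about half of the lost intervention patients died against a fifth of the lost controls. A 16% v 20% result is more fragile, tipping at about 31%. That level is close to the 30% in-hospital mortality that Section {14} reports for this setting, but it still requires higher mortality among the lost in the intervention arm than in control. This is a worthwhile, inexpensive correction and not a threat to the unadjusted primary analysis.

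**What to change.** Limit the sentence in Section {20c} to the primary outcome in the primary analysis. Then state:

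1. Adjusted models keep all randomised participants. Missing baseline covariates are handled by a rule set without reference to outcome: mean or median fill with a missing indicator, or multiple imputation.
2. Censoring at last assessment remains the primary handling of unknown vital status. One tipping-point sensitivity analysis varies mortality among the lost separately by arm.

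The cost is one extra table, some programming and a protocol wording amendment, which Section {25} sends through ethical and regulatory review. Recruitment ended on 30 June 2024 and the article does not say whether analysis has begun, so the change should be dated and, if still possible, made before the arms are compared. The unadjusted primary analysis is unchanged.

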### Plans to give access to the full protocol, participant level-data and statistical code {31c}

A clean de-identified database will be provided as publicly available (‘open access’) or upon reasonable request, after the final study publication is published, as per the relevant medical journal regulations. Anonymised data from the study will be shared upon request. Request for use of the study data will be assessed by the KEMRI-CGMRC Data Governance Committee to safeguard interests of participants and their communities.

## Oversight and monitoring

### Composition of the coordinating center and trial steering committee {5d}

An independent trial steering committee (TSC) has been convened for the trial. The TSC advise on the protocol, trial’s implementation including review of timeliness and recruitment and, any interim analyses to be conducted. The TSC meets quarterly during the trial duration. 

The trial has a coordination team that includes the co-principal investigators, a research medical officer, a trial coordinator and a data manager. The coordination team manages the trial’s day-to-day running, conduct safety monitoring and ensure ethical standards are maintained during the trial.

### Composition of the data monitoring committee, its role and reporting structure {21a}

An independent Data and Safety Monitoring Board (DSMB) has been convened for the trial. The main aim of the DSMB is to ensure safety of the trial’s participants through regular review of trial safety data. DSMB reports are shared with the trial investigators, the TSC and sponsor. The DSMB has five members including one chair. The membership includes a diverse representation of experts, including, specialists in clinical trials, physicians, and statisticians. The trial’s DSMB charter further details the role of the DSMB, its membership, frequency of meetings and reporting structure.

### Adverse event reporting and harms {22}

The corticosteroids to be used in this clinical trial have been used for many decades and are not expected to result in any serious unexpected adverse reactions. Adverse events (AEs) and serious adverse events (SAEs) will be defined in accordance with the International Conference on Harmonization (ICH) Guidelines for Good Clinical Practice.

Trial staff and hospital staff will review participant health status daily while in-patient and solicit for expected adverse events. Patients will be advised verbally and in writing (study information sheet) that they should inform hospital staff if they develop any change in their medical condition during their hospitalization and after discharge. Patients will in addition be given the phone number of the local trial clinical officers.

Any AE will be evaluated for seriousness, relatedness, severity, and expectedness by the study clinician. Where further medical attention is needed, the study team will organise referral and emergency admission to the nearest health facility.

All AEs that are not serious will not be reported individually but will be recorded in the CRF and summarised in an annual safety report.

All SAEs will be reported individually using an SAE form including an assessment of relatedness, severity, and expectedness.

The principal investigator (PI) or designee will be responsible for safety monitoring and reporting SAEs to the DSMB, Sponsor, ethics committees and regulatory authorities as appropriate. Those that are life-threatening, serious and unexpected or suspected to be causally related to study medication will be reported to the DSMB, Sponsor and product manufacturers.

### Frequency and plans for auditing trial conduct {23}

Trial monitoring will be conducted by independent staff from the clinical trials facility (CTF) at the KEMRI-CGMRC in Kilifi. The focus of monitoring will be on those factors critical to quality (i.e. the safety of the participants and the reliability of trial results). The frequency of monitoring will be decided by the monitoring team. Monitoring reports will be shared with the sponsor and regulator during annual reports.

### Plans for communicating important protocol amendments to relevant parties (e.g. trial participants, ethical committees) {25}

All protocol amendments will be discussed with the investigators and site leads. They will then be subjected to ethical and regulatory review before adoption.

The trial’s DSMB and TSC will be made aware of any changes to the protocol and associated forms.

## Dissemination plans {31a}

The results of the trial will be reported in a clinical study report generated by the sponsor, containing CRF data, laboratory data and safety data. The sponsor will register and disclose the existence of the results of the clinical trial on an international clinical trials registry in accordance with good practice. Individual participant identifiers will not be used in any publication of results.

Results will be published in an open access format, consistent with Good Publication Practices, the International Committee of Medical Journal Editors guidelines and funder requirements. The primary trial results will be published including all investigators meeting ICJME criteria as authors. Local investigators will take prominent roles in the primary trial results write-up. Secondary analyses will also be developed as part of KEMRI-CGMRC’s commitment to capacity development to ensure that co-investigators have additional opportunities for individual scientific output.

Results will be disseminated to the Kenya Ministry of Health, the Kenya Medical Association, all of the participating hospitals and other relevant stakeholders e.g., the WHO. Results will also be disseminated locally in the areas where the study was conducted and participants will be invited to meetings to receive feedback on the trial outcomes.

### Ethics approval and consent to participate {24}

Kenya Medical Research Institute - Scientific Ethics Review Unit (KEMRI-SERU) - SERU 4319

Pharmacy and Poisons Board of Kenya (PPB) – PPB/ECCT 21/11/02/2022(103)

Oxford tropical Research Ethics Committee (OxTREC) – OxTREC 4–22

National Commission for Science, Technology and Innovation (NACOSTI) – NACOSTI/P/22/16486

Written, informed consent to participate will be obtained from all participants or their legally authorized representatives.

Deferred written informed consent will be sought for patients too unwell to provide consent within 48 hours of admission if written assent is provided by their legally authorized representatives.

### Consent for publication {32}

The investigators are willing to provide a model consent form on request

## Discussion

Despite community acquired pneumonia being a major cause of mortality among adults in low- and middle-income countries, very few clinical trials that are relevant to this setting have been conducted. The SONIA trial is a pragmatic randomized clinical trial that aims to determine whether the addition of corticosteroids to standard of care in patients with community-acquired pneumonia reduces mortality. The trial is being conducted in public hospitals in Kenya, many of which have not participated in research activities before. However as has been argued previously, in order to generate results that are widely applicable to the real world, clinical trials need to be as simple as possible
^
29
^. The pragmatic nature of the SONIA trial makes it easy to conduct it in the course of routine clinical work without exerting too much extra work on staff at the participating hospitals, while at the same time aiming to generate reliable results that are relevant to the setting. The clinical question being addressed is highly relevant to the patients, eligibility criteria are simple, the intervention readily available, and follow up procedures easy to implement.

## Study status

Current Protocol – Version 2.0 dated 01 February 2022

Recruitment start date – 25 April 2022

Actual recruitment end date – 30 June 2024

## Abbreviations

AE                    Adverse Event

ATP                  According-to-protocol

CAP                 Community Acquired Pneumonia

CFR                  Code of Federal Regulations

CI                     Confidence Interval

CME                 Continuous Medical Education

COVID-19        Corona Virus Disease 2019

CRF                  Case Report Form

CTF                  Clinical Trials Facility

DSMB              Data and Safety Monitoring Board

ERC                 Ethics Review Committee

GCP                 Good Clinical Practice

ICF                  Informed Consent Form

ICH                  International Conference on Harmonization

IgG                  Immunoglobulin G

IRB                  Institutional Review Board

ISF                   Investigator site file

ITT                  Intention to treat

IU                    International Units

KEMRI            Kenya Medical Research Institute

LAR                 Legally authorized representative

LMIC                Low- and Middle-Income Countries

NRA                 National regulatory authority

OxTREC           Oxford Tropical Research Ethics Committee

PI                      Principal Investigator

PIS                    Patient information sheet

PP                      Per Protocol

SAE                    Serious Adverse Event

SAP                    Statistical Analysis Plan

SERU                  Scientific Ethics Review Unit

SOP                    Standard operating procedure

SUSAR               Suspected unexpected serious adverse reaction

TSC                    Trial Steering Committee

WHO                   World Health Organization

## Data Availability

A clean de-identified database will be provided as publicly available (‘open access’) or upon reasonable request, after the final study publication is published, as per the relevant medical journal regulations. Information collected or generated during this study may be anonymised for use to support health policies and/or further research. Any further research using information from this study must first be approved by a local or national expert committee to make sure that the interests of participants and their communities are protected. The protocol’s SPIRIT checklist and flow diagram are available at
https://doi.org/10.5281/zenodo.7180419
